## Abstract

**Background:**

Some countries have experienced and may continue to experience severe devastation due to wars, epidemics, earthquakes, and other natural catastrophes. When individuals are exposed to specific psychological or physical traumas, they can develop stress-related disorders, which can lead to irreversible changes in the autonomic nervous system and the development of cardiovascular disorders. When subjected to a new stress test, traumatized participants or those previously exposed to trauma may show more pronounced behavioral changes, intolerance, and greater fatigue responses than before trauma exposure. To reduce the recurrence of trauma-associated responses, particularly among young people, it is necessary to implement preventive measures. Alternative approaches, including counseling, medication, phytotherapy, and other interventions, need to be developed. This study aims to examine how individuals cope with trauma-related situations using a biofeedback method that could be developed to manage stress-related responses. The emotional and psychological states of earthquake victims will be assessed using a protocol based on biomedical (neurocardiac) signals and the sound of the participants’ hearts. This sound will be delivered at a fixed frequency or in real time with allostatic auditory stimulation. This approach aims to induce a resonance that stabilizes the autonomic nervous system by providing biofeedback to participants.

**Methods:**

To examine different states, biological signals will be measured and recorded, including electrocardiography (ECG), phonocardiography (PCG), electrodermal activity (EDA), respiratory rhythm, and functional near-infrared spectroscopy (fNIRS). Statistical methods and deep learning models will be applied to process the collected data optimally and evaluate the results.

**Impact:**

This study aims to assess the medium- to long-term risk of trauma-induced stress among young individuals. The use of non-invasive sound therapy to evaluate its effects on the vagal nerve through cardiovascular responses and neural activity may provide biofeedback for these individuals.

**Clinical trial registration:**

https://clinicaltrials.gov/study/NCT06919055. The trial has been registered on www.ClinicalTrials.gov with registration number NCT06919055 on 17 March 2025 with the title “Biofeedback with Heart Sound Following Trauma (ALLOSTAT0001).”

## Background

1

People who have experienced a major earthquake, pandemic, or war often find themselves in an unstable situation, facing losses, disorganization, inability to remain in their homes, fear of another earthquake, pandemic, war, and air pollution. Young people who experience natural disasters and/or other traumatic events may develop stress-related disorders that are not always visible and may emerge over time (Scott and Weems, 2014). Furthermore, stressful life events, including those linked to natural disasters that cause trauma and stress, may precede neurocognitive disorders in people who experienced these events during their youth. In her study, Giannouli (2024) examines research conducted not only in older adults but also in animal models, as well as the associated neural mechanisms. Young people may not realize the seriousness of the situation in their daily lives. However, this may lead to changes in the autonomic nervous system and cardiac problems that cannot be adequately compensated for in the future. Adverse reactions can also be manifested by overactivity of the sympathetic nervous system or an inability of the parasympathetic system to stop overactivation. Therefore, studies assessing vagal tone at rest in young people are needed (Weems, 2015). There is growing evidence that treatments to reduce adverse outcomes and prepare young people to cope with stressful situations will improve emotional and physical health and wellbeing and provide wider societal benefits (Patron et al., 2021). The demographic and cultural differences across populations also have an impact in this regard. In this case, our study will aim to stabilize the autonomic nervous system in young people experiencing new stress.

The limitations of current stress treatments include side effects, addiction risk, time constraints, and lack of efficacy. Although cognitive therapy and psychopharmacological treatments are practical and complementary and alternative medical approaches are widely used, new and additional treatments are needed (Tegeler et al., 2023). There is evidence that listening to music may have a therapeutic effect in many areas, such as combating stress, anxiety, and sleep (Giannouli, 2017; Liu et al., 2016; Nakajima et al., 2016). Raglio and Vico suggested that the complexity of music should be simplified, the musical stimulus should be standardized, and the cultural dimension should be overcome and personalized (Adiasto et al., 2022; Raglio and Vico, 2017). Lee et al. converted certain frequencies ranging from 0.5 Hz to 48.5 Hz into audible sound in real time and then applied them to participants in the training group (Lee et al., 2019). On the other hand, the literature suggests that low-frequency sounds associated with electroencephalography (EEG) signals are suitable for treating insomnia (Gerdes et al., 2013; Guannan et al., 2023; Tegeler et al., 2023). Bhavsar et al. examined the applications of musical neurofeedback in the literature. This study presents the comparative effects of musical applications in EEG-based neurofeedback for diagnosis, treatment, and improvement. Neurological disorders after various traumas (in the EEG alpha, beta, and theta bands) were addressed through music-based neurorehabilitation, and changes in the emotional states of the participants were examined with positive results. The study also examined the effect of music on physiological parameters, such as heart rate and blood pressure, among others (Bhavsar et al., 2024). Neurofeedback is a promising approach that allows feedback to guide brain responses. The current systems are far from an individualized approach. A study presented an individualized system by testing gamma-band activity induced by auditory stimulation (Mockevicius et al., 2024). Gouda and Andrysek investigated the applicability of the Rhythmic Auditory Stimulation technique for rehabilitating temporal gait asymmetry. The study shows that the Rhythmic Auditory Stimulation Biofeedback system is promising for correcting abnormalities in gait symmetry and lower extremity disorders such as gait disorders (Gouda and Andrysek, 2024). It has been observed that such sounds are also suitable for post-traumatic stress (Lee et al., 2019).

Mechanical, vibroacoustic, or electrical/magnetic stimuli, applied in a pulsed manner to the body or to cells at frequencies close to the heart rate (approximately 1 to 3 Hz), have yielded positive results, highlighting the possible existence of a resonance effect (Kim et al., 2023; Zabrecky et al., 2020). Low-frequency mechanical stimulation has been shown to have significant effects on parasympathetic activity and heart rate variability, notably through the activation of the vagus nerve via low-frequency vibrations (Hauser et al., 2025) and transcutaneous electrical stimulation at frequencies as low as 1 Hz (Yokota et al., 2022), although these more recent studies report a more modest effect than at higher frequencies. Kim et al. aimed to prevent autonomic nervous system imbalance resulting from dynamic movement. They used average heart rate resonance (aHRR) as an auditory stimulus and investigated its role in improving the stability and homeostasis of the autonomic nervous system (ANS). The effect of aHRR on the ANS was analyzed using photoplethysmogram data collected from 22 participants by examining heart rate variability in the temporal and frequency domains. These results suggest that aHRR may influence the cardiovascular system by facilitating physiological changes that occur during dynamic movement (Kim et al., 2023). However, these studies did not replicate a stressful situation or examine the neurocardiac axis, nor did they allow for real-time monitoring of brain function and emotional and cognitive changes using fNIRS measurements. Our study proposes the exploratory hypothesis that auditory stimulation close to the natural heart rate (<3 Hz) could activate associated vagal afferent mechanisms; however, the effect of real-time heart sounds has not yet been directly tested as an auditory stimulus in the existing literature.

The body makes adjustments to maintain homeostatic balance through allostatic mechanisms; however, when stress exposure becomes exaggerated and prolonged, it may result in the failure or dysregulation of these systems (Suvarna et al., 2020). All of these conditions can be associated with autonomic imbalance, with an increase in the sympathetic nervous system (Nagai et al., 2022). The neurocardiac axis provides a physiological explanation linking psycho-emotional stressors to cardiac events (Fioranelli et al., 2018). In the neurocardiac axis, biofeedback can promote synchronization and resonance with an individual’s physiological rhythm. Kim et al. used mean heart rate resonance as a sound stimulus during dynamic movements in healthy subjects (Kim et al., 2023). However, this study did not examine oxygenated and deoxygenated hemoglobin (HbR) in different brain lobes using fNIRS measurements. Coulter et al. investigated the use of the heart rate variability biofeedback technique in managing high stress levels among people with autism spectrum disorder (Coulter et al., 2024). In patients with type 2 diabetes mellitus, the sympathetic and parasympathetic systems exhibit imbalanced functioning. This causes weakness in cardiac activity and glycemic control. In addition, the emotional state of patients may also be negatively affected. Wu et al. used the heart rate variability biofeedback technique in their study and proved its effect on these adverse outcomes (Wu et al., 2024). Ramakumar and Sama (2024) examined the effect of heart rate bariability biofeedback on perioperative stress, recovery, and anesthesia management in surgical patients. Heart rate variability is a physiological marker through which the positive or negative consequences of the activities of the autonomic nervous system can be observed. The resonance state is primarily associated with vagal nerve activity (Ramakumar and Sama, 2024). Some studies have reported improvements in insomnia, postnatal depression, stress, and anxiety disorders with biofeedback (Blase et al., 2021; Gerdes et al., 2013; Lee et al., 2019; Tegeler et al., 2023).

In the literature, stress generation in individuals can be achieved through the mental arithmetic (Goswami et al., 2012; Mezzacappa et al., 2001), social noise (Liu et al., 2016; Nakajima et al., 2016), and dynamic movement (Kim et al., 2023; Lampert, 2015). The recovery heart rate of subjects performing mental arithmetic tasks was lower than the baseline heart rate (Goswami et al., 2010), and the heart period variability was higher than the baseline. Cardiovascular recovery from stress is associated with increased vagal modulation despite sympathetic activation. These findings confirm the association between vagal reflex attenuation and cardiovascular disease risk (Mezzacappa et al., 2001). In this study, we will introduce new mental stress levels (Lampert, 2015) for younger individuals.

In this context, there have not been many studies on new techniques, such as deep learning techniques currently used in signal and image processing. As part of this study, statistical tools will first be used, followed by deep learning models, to process the data collected and evaluate the results as comprehensively as possible. Explainable artificial intelligence (XAI) techniques will enable this approach to be presented in a transparent manner (Ong et al., 2021). Thus, the interpretability of the selected models can contribute to the design of efficient classifiers.

Our study investigates how individuals can cope with such stress-related disorders and what kind of biofeedback can be developed to manage them. In order to facilitate the balancing and self-calibration of neuronal oscillations, this study, within the scope of the biofeedback study, will create awareness by presenting the participant’s heart sound as a warning in real time. As the heart rhythm increases, the person will perceive that he/she needs to self-regulate and calm down through biofeedback, thereby improving stress management and affecting the autonomic nervous system. In summary, allostatic regulation and autonomic balancing of neural oscillations in trauma-exposed individuals will be explored non-invasively through biofeedback.

## Objectives

2

The ALLOSTAT0001 project aims to analyze and investigate cardiovascular risk in young people who have experienced trauma, such as that caused by an earthquake. The aim of this study is to develop biofeedback for non-invasive relaxation and autonomic stabilization of neural oscillations in young participants with post-traumatic stress. Using a framework that employs mental stress tasks and auditory stimuli derived from heart sounds, we will investigate whether biofeedback can be enhanced by supporting allostatic regulation. This may lead to synchronization and resonance with an individual’s physiological rhythm.

The study will also provide a better understanding of the physiological responses (electrodermal activity and neuronal activity) of young participants undergoing another type of mental stress. In this context, young participants’ emotional and psychological states will be observed using biomedical signals, and processing and relaxation states will be derived from these signals. Repeated measurements over a given period will provide valuable information regarding changes in cardiovascular and psychological risk markers over time.

While some studies have attempted to reduce the allostatic load by applying auditory stimuli derived from electroencephalogram signals or stimuli with a musical tone, there is currently very little information on applying auditory stimuli derived from heart rate. The use of stimuli with a frequency that has the potential to induce resonance and measurements of oxygenation in the prefrontal cerebral area using the fNIRS technique enhances the novelty of the project and underlines its strengths.

In this interdisciplinary study, we aim to use the measured heartbeat sound as an auditory stimulus and examine its effect on the stability of the autonomic nervous system in young participants exposed to mental stress. A young person entering a new mental stress environment will be given their heart sound (or a metronome synchronized with their heart rhythm while calm) or a real-time heart sound as an auditory stimulus. According to the proposed hypothesis, it is assumed that this will produce a resonance effect in the participant and promote relaxation. Typically, it is believed that the average heart rate is the individual’s intrinsic resonant frequency due to the influence of the autonomic neural system (ANS). In other words, allostatic acoustic stimulation at the same frequency as the individual’s heart rate will transmit auditory information and may activate the young participant’s brainstem.

First, statistical tools and then deep learning models will be used to process the collected data optimally and evaluate the results. Explainable artificial intelligence (XAI) techniques will support the transparent interpretation of this approach. With this protocol, we aim to use signals to show the correlation and causality between the stimulus and psychophysiological response.

The aim of this study is to contribute to the literature and scientific community by obtaining research results at an international level and by clarifying unexplored elements of a topic that has not been studied in this context previously. The collected parameters have great potential for improving the prediction of future cardiovascular and psychological events in young people, adults, and children. The type of trauma addressed will not only be the experience of an earthquake but also exposure to other natural disasters, epidemics, or wars.

The information obtained from this project is important for developing guidelines and recommendations for managing the health of young people at risk. The results of the ALLOSTAT0001 project will also contribute to the search for solutions to enable young people who have suffered significant trauma to lead healthy lives over a long term. Early self-therapy using individual efforts and natural methods may be highly effective in minimizing the need for medication or hospitalization.

## Methods/design

3

The Project has received ethics approval from Harran University with the decision of the clinical research ethics committee. The study was registered under the number E-76244175-050.04-346993, on the 10th of June 2024. The study will be conducted at Kahramanmaras Sütçü İmam University in Türkiye. The study was subsequently registered with www.ClinicalTrials.gov under the registration number NCT06919055 in March 2025 and follows the Standard Protocol Items: Recommendations for Interventional Trials (SPIRIT) reporting guidelines (Chan et al., 2013). All items from the World Health Organization Trial Registration Data Set are summarized in Table 1 according to the SPIRIT reporting guidelines. Data collection began in December 2024 and completed by 30 June 2025.

**Table 1 tab1:** Items from the World Health Organization trial registration dataset.

Section/item	Information
Primary Registry and Trial Identifying Number	ClinicalTrials.gov, NCT06919055
Date of registration in primary registry	17 March, 2025.
Secondary identifying numbers	124S102
Source(s) of monetary or material support	The Scientific and Technological Research Council of Türkiye (TÜBİTAK)
Primary Sponsor	[name] and [name]
Secondary sponsor (s)	[name], [name]
Contact for public queries	[name], [contact]
Contact for scientific queries	[name], [contact] and [name] [contact]
Public title	Allostat0001
Scientific title	Biofeedback with Heart Sound Following Trauma
Countries of recruitment	Turkey
Health condition(s) or problem(s) studied	This study aims to examine how individuals cope with trauma-related situations using a biofeedback method, which could be developed to manage stress-related coping.
Intervention(s)	1. Control 2. Heart sound stimulation 3. Metronome with ECG rate stimulation
Key inclusion and exclusion criteria	36 earthquake survivor university students aged between 20 and 25 years will participate in the experiment. Participants will be healthy, non-obese men (*n* = 18) and women (*n* = 18). In particular, all participants should have experienced an earthquake disaster in the local region. All participants should be free of any chronic or acute infection, neurological, psychiatric, and/or cardiovascular disease. They must be non-smokers, have no alcohol or drug addiction, and not be under any medical treatment. Pregnant or breastfeeding women will not be included in the study.
Study type	Allocation: non-randomized Intervention model: parallel assignment Primary purpose: treatment
Date of first enrollment	December, 2024.
Target sample size	36
Recruitment status	Recruiting.
Primary outcome(s)	Method of measurement: Biopotentials (ECG, PCG, EDA, fNIRS, respiratory rhythm) Timepoint: pre-treatment, post-treatment, and follow-up.
Key secondary outcomes	Changes in neuroimaging measures Timepoint: pre-treatment, post-treatment, and follow-up. Changes in biopotential measures Timepoint: pre-treatment, post-treatment, and follow-up.
Ethics Review	This project received ethical approval from Harran University with the decision of the clinical research ethics committee on 03 July 2024.
Completion Date	October, 2025

The SPIRIT reporting guidelines recommend these items to be included in trial protocols to provide a brief, structured overview of a trial.

Our study is a non-randomized, parallel-group cohort study. Patients were assigned to a group in the chronological order of enrollment in the study. Therefore, consecutive sampling was used for allocation concealment. The inclusion and exclusion criteria will be applied uniformly to all patients, regardless of group, without exception. At inclusion, baseline characteristics will be compared between groups, including age, sex, and whether participants experienced the earthquake as a traumatic event. The comparability of the groups at inclusion will be verified by ensuring that there are no significant differences between groups.

In order to carry out this study, the following basic measurements—sex, age, height, weight, blood pressure, etc.—and relative measurements derived from the basic measurements will be extracted. In this context, the cardiovascular, emotional, and psychological states of earthquake survivors will be observed through biomedical signals. Electrocardiography (ECG), respiratory rhythm, and electrodermal activity will be measured to evaluate the autonomic nervous system, particularly the parasympathetic nervous system. A metronome based on the heart rate derived from the ECG and the measured phonocardiogram signal will be used for auditory stimulation. Our protocol will calculate and use the biological markers of heart rate variability (HRV), including low-frequency band (LF), high-frequency band (HF), LF/HF, standard deviation of NN intervals (SDNN), and root mean square of successive differences (RMSSD). The fNIRS device will measure changes in oxygenated and deoxygenated hemoglobin concentrations in the cortical brain structure before and during mental exertion. The sound of a heartbeat will be evaluated to determine its effects on fNIRS results in the prefrontal cortex during relaxation and stress.

Each participant will have 390 min of experimental activity, including 330 min of measurements.

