Deep learning techniques and statistical analyses will be used to examine the causality between the generated stress, given warning, and measurements. The data will be processed as a time series or converted into images in our study. Each participant will have 390 min of experimental activity, including 330 min of measurement time.

Transfer learning from an existing pretrained convolutional neural networks (CNNs) will be applied for the acquired data. If there is sufficient data to train a new neural network, the formation of a new network architecture is considered for the sustainability of the protocol.

Explainable artificial intelligence techniques will be used to analyze the data attributes used by the network.

Below are the protocol diagrams to be applied before the first session, throughout the 10 intervention sessions, and after 4 weeks (Figures 1–3).

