This study did not include an acoustically equivalent sham arm (scrambled sound), thus limiting the ability to completely isolate the specific effects of real-time heart sounds from the non-specific effects of listening and directed attention. However, the comparison between the silent, metronome, and heart-sound arms provided a partial separation of these effects. The main objective of this study is to explore the overall efficacy of the intervention under real-world conditions rather than to isolate its precise mechanism of action. Future studies incorporating an acoustically matched sham arm are necessary to confirm the specificity of the proposed mechanism.

Another limitation is that the first session, the subsequent 10 sessions, and the day of the follow-up evaluation for all groups may not be conducted in the same season. As seasons are known to affect physiological parameters (Goswami et al., 2021; Goswami et al., 2020; Trozic et al., 2020), we will endeavor to conduct most recordings during a single season. This should prevent differences in ECG signals owing to seasonal changes.

Because of the front-end morphology of each participant, during measurements with fNIRS, not all 16 channels can produce significant signals. We will, therefore, use the maximum number of active channels for all participants. We will use a headband or cap to improve contact with the prefrontal area for all participants. At worst, 12 channels will provide sufficient information about the right, central, and left prefrontal cortex activity.

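### Assignment by order of enrolment is called allocation concealment, which it is not, so the between-arm comparison cannot support the aim of showing causality

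*Protocol article*

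**What the plan says.** All places are in the Protocol article.

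- **Design (section 3, Methods/design).** "Our study is a non-randomized, parallel-group cohort study". Table 1 also gives the allocation as non-randomised.
- **Assignment (same section).** "Patients were assigned to a group in the chronological order of enrollment in the study. Therefore, consecutive sampling was used for allocation concealment". The article does not say whether the three arms were filled one after another or participants were rotated through them.
- **Comparability (same section).** Baseline characteristics, among them age and sex, are compared between groups, and the absence of significant differences is taken as verification.
- **Aim (section 2, Objectives).** "we aim to use signals to show the correlation and causality between the stimulus and psychophysiological response". Section 3.1.2 adds: "Deep learning techniques and statistical analyses will be used to examine the causality between the generated stress, given warning, and measurements".
- **Timing (section 3).** "Data collection began in December 2024 and completed by 30 June 2025".
- **Season (section 5, Limitations).** The article accepts that season affects physiological parameters and that the groups may not be recorded in the same season. Its remedy is: "we will endeavor to conduct most recordings during a single season. This should prevent differences in ECG signals owing to seasonal changes".
- **Primary analysis (section 3.5.1).** RMSSD, HF and LF at the final session are compared with the first session, by a linear mixed model with group and time as fixed effects or by ANCOVA.

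Section 5 discusses the missing sham arm, recruitment, missing data and season. It does not list non-random, foreseeable assignment.

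**The concern.** Allocation concealment means that the person deciding whether to enrol a volunteer cannot know which arm that volunteer would join. Consecutive sampling is a recruitment rule and has no bearing on this. An order-of-enrolment rule works against concealment, so the inference drawn with the word 'therefore' does not follow.

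The article leaves room for selection at this step. Volunteers are interviewed and medically examined before acceptance (section 3.1.1), up to 10 backup participants may be added, and people who stay in the city over the holiday get scheduling priority (section 5). Whom to take, and when, can thus be decided with the next arm known. A difference between arms might then reflect who was enrolled rather than the sound stimulus. A reader told that assignment was concealed would discount that explanation and give the causal aim more credit than the design allows.

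**Working it through.** The plan states no figure on this point, so there is none to reproduce. The main step is logical. The calculations show how much the safeguards offered can carry, and when season matters.

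**1. Foreseeability.** Let i be the enrolment number, k the arm size, and N = 3k. If arms are filled in turn, participants 1 to k join one arm, k+1 to 2k the next, and the rest the third. If rotated, the arm is fixed by the remainder of i divided by 3. Either way the arm is a fixed function of i, so anyone who knows the rule and the count knows the next arm. The error therefore stands under both readings.

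**2. Can the baseline check replace concealment?** Inputs: 10 per arm (section 3.1.2) or 12 per arm (section 3.1.1, and 36/3). Assumed: two-sided alpha 0.05 and a two-sample t-test.

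| True imbalance | Power, n = 10 | Power, n = 12 |
|---|---|---|
| 0.3 SD | 10% | 11% |
| 0.5 SD | 19% | 22% |
| 0.8 SD | 40% | 47% |
| 1.0 SD | 56% | 65% |

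An imbalance must reach about 1.32 SD (n = 10) or 1.20 SD (n = 12) to be detected with 80% power. A non-significant test verifies little.

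**3. Arm and calendar time.** Assumed: a start on 1 December 2024 (the text gives only the month) and evenly spaced enrolment. To 30 June 2025 is 211 days. Enrolment must close before the end: 211 − 28 = 183 days if only the 4 weeks of sessions are allowed for, or 211 − 56 = 155 days with the 4-week follow-up as well. Call this E. The spacing is E/(N − 1).

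- Filled in turn, gap between mean dates of first and third arm = 2kE/(N − 1). N = 36, E = 155: 24 × 155/35 = 106 days. N = 30, E = 183: 20 × 183/29 = 126 days.
- Rotated, gap = 2E/(N − 1). N = 36, E = 155: 310/35 = 8.9 days. N = 30, E = 183: 366/29 = 12.6 days.
- Total sum of squares of dates, in spacing units = N(N² − 1)/12: 2247.5 for N = 30, 3885 for N = 36.
- Share between arms, filled in turn = 2k³/total: 2000/2247.5 = 0.89 and 3456/3885 = 0.89.
- Share between arms, rotated = 2k/total: 20/2247.5 = 0.009 and 24/3885 = 0.006.

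Filled in turn, a linear date term has a variance inflation of 1/(1 − 0.89) ≈ 9. It could hardly be separated from arm.

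**4. What reaches the primary comparison.** Let s(t) be the seasonal level on day t. First to final session takes about 4 weeks, so seasonal change within a participant is s(t + 28) − s(t). The arms differ in change only by the difference in that quantity: nothing if s is linear, otherwise the difference in drift. A stable difference in level cancels in the change. Under ANCOVA with baseline slope b between 0 and 1, a fraction (1 − b) of it remains. Beyond this, season matters if it modifies the effect of the stimulus. The 106 to 126 days are therefore not the size of a bias.

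**The case against.** The best defence is that the article is open about its design. It says non-randomised twice, calls the outcomes pilot outcomes for estimating effect size and variance, and describes the work as preliminary. Causality is worded as an aim or something to examine, not as a result. The sentence in section 3.1.2 also covers the induced stress, which every arm receives and which is studied within participants, so that part does not depend on assignment. Season is disclosed as a limitation, comparison with the first session already handles most of the baseline level, and a full covariate list may properly be left to an analysis plan that is not shown.

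Most of this stands, and it sets the limits of the point. A reader might infer that arm and season are confounded by some hundred days, or that the plan asserts a proven causal effect. The documents support neither. The sequence is not stated, rotation would nearly balance dates, the primary outcome is a change over about 4 weeks, and causality is only an aim. The absence of an enrolment-date term from section 3.5.1 is not an error in itself.

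What the defence does not reach is the concealment sentence. Calling a study non-randomised does not tell the reader that assignment was foreseeable when the same paragraph says it was concealed.

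**Conclusion.** The statement on allocation concealment is wrong as written and must be corrected. It reports protection against selection bias that assignment by order of enrolment cannot give, under either reading of that order. As a result, the between-arm comparison supports exploratory association and not the causal aim of section 2. This conclusion rests on the text alone.

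The seasonal part is conditional. With even enrolment from 1 December, arm accounts for about 89% of the variance in enrolment date if arms were filled in turn and for under 1% if they were rotated. Even in the first case the threat to the first-to-final-session change is differential drift or effect modification, and the documents give nothing from which to size either. The assurance in section 5 that seasonal ECG differences should be prevented is too strong for collection that ran from December to the end of June and rests only on an intention.

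**What to change.** Data collection is reported as completed (section 3), although Table 1 still lists the trial as recruiting. The remedy is therefore one of wording, reporting and one sensitivity analysis.

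1. In section 3, delete the concealment claim. State that assignment was sequential, foreseeable and non-randomised, and say whether arms were filled in turn or rotated.
2. In section 5, list this as a limitation.
3. In section 2, and in section 3.1.2 as far as the sound stimulus is concerned, replace causality with exploratory association. Apply the same limit to the classification of control against treatment in sections 3.4.1 and 3.4.2.
4. Report session dates by arm. In section 5, replace the assurance about season with a statement that seasonal differences may remain.
5. If arms were rotated, add one linear enrolment-date term to the primary model as a sensitivity analysis. If they were filled in turn, state that arm and calendar period cannot be separated, and do not rely on covariate adjustment.

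The cost is a few sentences, a table of dates and, under rotation, 1 degree of freedom in a secondary fit. The price in substance is a weaker between-arm conclusion, which is all the design can carry.
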